### Recruitment, Screening, and Gaining Informed Consent

Each participating mental health care center will be responsible for identifying potential patients who meet eligibility criteria for the study. Identification of potential participants will occur at the point of triage or initial assessment, depending on the specific procedures of the participating centers, as part of routine clinical care. Specifically, the clinician conducting initial assessments of patients referred for mood problems will consider the inclusion and exclusion criteria for the study. It is acknowledged that the assessing clinician may identify exclusion criteria or other factors that could deem a patient unsuitable for the study (eg, risk of possible injury to therapists, imminent suicidal risk) even if the patient meets the inclusion criteria. Unless this is the case, the clinician will offer the patient a brief verbal introduction to the study, constituting a preliminary invitation to participate. The clinician will provide the patient with a participant information sheet to read and keep. The participant information sheet will include age- and culturally appropriate material explaining the study and what involvement in the study would entail at that particular site. Clinicians then confirm whether the patient consents to being contacted by a researcher from the research team, who will then discuss the study in more detail with the patient. Patients will be given ample time (minimum 48 hours) to think about the information provided and can request more time to think about the study before consenting to further contact from the researcher. If a patient verbally consents to being contacted by a research assistant (RA), the clinician informs the research team of this decision and provides relevant contact information.

An RA will contact potential participants no less than 48 hours after they receive information about the study from participating centers, to explain what participation might involve and to arrange an appointment at the mental health center. A study identification number will be assigned to the participant, and from this point on, the participant will be referred to only by this number, and their collected data will be labeled with it. After the participant has provided explicit and written informed consent, an RA will administer the SCID-5-CT interview and the PHQ-9 and will assess all other inclusion/exclusion criteria. When all the measures have been completed, and study eligibility has been confirmed at baseline (ie, checks for inclusion/exclusion criteria have been confirmed), an RA will provide the trial coordinator (TC) with the details required to randomize the participant to one of the four conditions.

For the qualitative substudy, an RA will invite (first via email and then followed up by telephone) all patients who received blended treatment in the BLENDED trial who are beyond the 6-month follow-up assessment to find out whether they are interested in participating in an interview study focusing on their experience of blended psychotherapy. A minimum of 48 hours will be allowed between the initial contact with the participant and confirmation of their participation (by telephone or email) and the participant being approached again by the RA. An information leaflet and an additional informed consent form (ICF) will be sent by email to the patient following this first contact. This schedule is to allow sufficient time for individuals to consider and discuss participation in the substudy with any party they may choose to consult. An RA will confirm with the potential participant that this time frame has been sufficient and allow additional time if requested. As the substudy will be conducted online and not at the mental health care centers, patients will be asked in a separate contact to sign and email the ICF to the research team; after receipt, the RA will sign the ICF and return the fully signed ICF to the patient. As mentioned earlier, eligibility (ie, whether they found blended psychotherapy helpful or not) will be determined based on patients’ self-reported levels of helpfulness of blended treatment when they are approached to participate in this study. If a patient is eligible for the qualitative study, an RA will contact the patient again to schedule an online interview. For the focus group study with therapists, a similar procedure will be followed to obtain informed consent from the therapists.

### Randomization

This trial will use stratified and automated randomization of participants to one of four conditions in permuted blocks built into the electronic Case Report Form (eCRF). Stratification will be carried out in 2 stages. At stage 1, patients will be randomized to therapists within each participating center, using permuted blocks to ensure that the maximum difference of trial caseload for therapists within the same center is on average 2 patients. As each therapist will provide only either CBT or PDT, stage 1 implicitly allocates patients to the type of therapy. At stage 2, patients will be randomized to either FTF or blended care, again using permuted blocks such that the maximum difference in the number of FTF and blended therapy patients for each therapist will be 2 patients at any one point in time. Participant randomization will be initiated centrally by the TC, following the completion of the eligibility assessment (screening) by the RA and of the baseline measures by the participant, and before commencement of any trial intervention. As randomization will be performed using an automated web-based randomization algorithm built into the eCRF, which sends an automated email to the therapist, this will ensure that the RA remains blind to the treatment condition to which the patient is randomized.

This 2-stage stratified randomization scheme ensures balance for the comparison of FTF and blended therapy with respect to participating centers and therapists. The scheme will also promote, although not guarantee, balance with respect to any patient-level prognostic factors whose distribution varies between the patient populations of the centers (eg, age).

### Interventions

Both CBT and PDT, as offered in this trial, are based on manualized treatments developed in the context of the Improving Access to Psychological Therapies program in the United Kingdom [90,91]. FTF PDT and CBT consist of 16 FTF sessions, offered over a period of 4‐6 months. Blended PDT and CBT consist of 8 FTF sessions in combination with 8 online modules offered over a period of 4‐6 months and thus are similar in length to the FTF psychotherapies. Blended PDT and CBT are based on principles outlined in the manualized FTF psychotherapies and adapted for use in Flanders (Belgium) [17,92] in collaboration with service users and therapists as part of depressiehulp.be, a government-supported online platform that offers psychoeducation and (both unguided and guided) internet-delivered treatment for depression.

FTF sessions in FTF therapy and blended therapy are offered on a weekly and a 2-weekly basis, respectively, although with mutual agreement by the patient and therapist, the session frequency may deviate from the planned weekly or 2-weekly sessions. 

The content of FTF psychotherapy and blended therapy is very similar, as the treatments follow the same treatment manuals and treatment phases. The main difference between FTF and blended therapy is that in blended therapy, the therapists will be specifically trained to help motivate and encourage patients to complete the online modules between the FTF sessions, and to take the patient’s experience in completing each module as the starting point of the next FTF session. Hence, using the terminology introduced by Erbe et al [23], in this study, blended therapy will be offered in a fully integrated format, with digital modules being a core component of the treatment, FTF and digital sessions alternating, and blended treatment primarily being delivered in a standardized format for each patient, with some room for personalization of the treatment as detailed below.

FTF and blended PDT will be based on dynamic interpersonal therapy (DIT), an integrative evidence-based brief treatment for depression [90,93]. FTF DIT involves 16 weekly sessions of individual therapy, which formulates the presenting symptoms of depression as responses to interpersonal difficulties or perceived threats to attachments (loss and/or separation) and hence also as threats to the self. DIT conceptualizes depression in terms of an underlying temporary disorganization of the attachment system caused by current relationship problems, which in turn generates a range of distortions in thinking and feelings typical of depression. In DIT, there is a focus on both content and process. The content focus relates to the content of the individual dynamics that are associated with the onset and maintenance of depression. This focus helps the patient understand the connection between their presenting symptoms and what is happening in their relationships by identifying a core, repetitive pattern of relating that becomes the focus of the therapy, which is known as the interpersonal affective focus (IPAF). The process focus involves fostering the patient’s capacity for reflective functioning or mentalizing, as depression is typically associated with serious impairments in this capacity. In DIT, therapists use a range of interventions and techniques to restore the capacity for reflective functioning and to foster insight and change in the IPAF, consisting of supportive, mentalizing, insight-oriented, and directive interventions to empower the patient to translate insights obtained in therapy to their everyday life.

DIT consists of 3 phases. In the first phase (sessions 1‐3), the focus is on engaging and motivating the patient, assessing their presenting problems and dynamics, and collaboratively delineating the focus of the treatment (ie, the IPAF). The middle phase (sessions 4‐12) focuses on exploring how the patient’s typical pattern of relating to the self and others has led to feelings of depression, and how a change in this pattern might improve their mood. The ending phase (sessions 13‐16) is mainly concerned with empowering the patient to translate the insights they have gained in therapy to their everyday life.

The blended DIT program consists of the same 3 phases as FTF DIT: an exploration phase, a middle or working-through phase, and an ending phase. Instead of having 16 FTF sessions, patients in blended DIT are invited to complete online modules between 8 FTF sessions to explore the typical dynamics that are otherwise explored in the FTF sessions, and to discuss these in subsequent FTF sessions. The structure and phases of blended DIT are discussed in detail elsewhere [92].

FTF CBT involves 16 sessions offered over 4‐6 months. CBT is based on the assumption that depression is directly related to patterns of thinking [91,94]. Specifically, dysfunctional and often automatic patterns of thinking are assumed to be related to the onset and maintenance of depression. The overall goal of CBT is therefore to help a person recognize such patterns of thought, evaluate their validity, and replace them with more adaptive ways of thinking. In CBT, there is an emphasis not only on thinking (ie, “cognitive”), but also on doing and thus on changing behavior (“behavioral”).

Therapeutic sessions in FTF CBT are highly structured, with clear tasks and goals in each session. These tasks and goals draw from more classic cognitive behavioral principles, including psychoeducation about depression, cognitive restructuring (ie, identifying and challenging maladaptive thoughts and beliefs, fostering problem-solving capacities), behavioral activation, and relapse prevention. Therapists are allowed to use these principles flexibly in a manner that is tailored to the needs and preferences of individual patients. In this trial, a focus on more recent principles and techniques that have emerged within the CBT tradition, such as fostering mindfulness and applying principles of acceptance and commitment therapy, is also part of both FTF and blended CBT [91], but these are covered in only one FTF session or one online module.

The structure and focus of FTF CBT and blended CBT are similar. The only difference is that, as with FTF and blended PDT, in blended CBT, 8 of the sessions are replaced by online treatment modules, so that the focus in the FTF sessions is more on attending to the process components of treatment (ie, is the patient motivated? Do they understand the treatment rationale?) and on reviewing and discussing therapeutic progress. The structure and phases of blended CBT in this trial are discussed in detail elsewhere [17].

As a result of the early phase of the COVID-19 pandemic, various restrictions made physical attendance of screening and therapeutic sessions impossible. An amendment to the original trial protocol, replacing FTF in-person sessions with online sessions, was allowed during this phase of the pandemic and particularly during mandated restrictions on meeting in person (so-called “lockdowns;” see protocol amendments in Multimedia Appendix 1). Sensitivity analyses will address the potential effects on treatment outcomes of the fact that some patients had their FTF sessions online (see also the Statistical Analysis Plan section).

As this is a pragmatic trial, if the patient and therapist agree at the end of the treatment program that further treatment is necessary, the treatment can be continued with the same therapist, or the patient can be referred for additional and/or longer-term therapy based on mutual agreement between patient and therapist. In the former case, the number of additional sessions with the same therapist is recorded in the eCRF; in the latter case, additional psychotherapy is monitored using the TIC-P.

Therapists will be certified CBT and PDT psychotherapists (psychiatrists or psychologists), who must have completed a postgraduate psychotherapy training of 3‐4 years. In addition, they will receive a 4-day training program in manualized FTF and blended CBT or PDT delivered by certified trainers in CBT and PDT, respectively. They will also receive 2-weekly small-group supervision of at least 2 patients by certified CBT and PDT supervisors.

### Discontinuation and Withdrawal

Participants can withdraw from the study for any reason at any given time. Therapists can propose to withdraw a patient from the study (1) if they are of the opinion that a patient risks serious deterioration and nonresponse to the treatment to which they have been allocated (ie, the patient needs longer-term treatment), and/or (2) if it becomes clear that the patient does not meet inclusion criteria or meets one or more exclusion criteria, despite initial screening and assessment (eg, the patient does have severe personality disorder), and/or (3) if participation of the patient in the study seriously interferes with treatment (eg, the patient is overly burdened by having to complete assessments). In all of these cases, the therapist needs to discuss the option of withdrawal from the study with the patient and must seek advice from a site supervisor and from the chief investigator. Patients who withdraw from the study for any reason are not replaced.

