##### Primary and Secondary Outcome Analysis

The primary analysis will be an ITT analysis, that is, all participants will be analyzed as randomized, even if they dropped out of treatment or changed treatment during the study period. The primary endpoint is 6 months after the end of treatment. The analysis will focus on the difference between the blended and FTF groups at the primary endpoint:

Adjusting for patients’ baseline BDI-II score.Adjusting for therapy type (CBT or PDT).Taking into account between-therapist variation.Taking into account variation between treatment centers (as a fixed effect).

A linear mixed-effects model (3-level ANCOVA, with therapists, time points, and patients as levels) will be estimated to investigate the null hypothesis that blended treatment yields inferior outcomes to FTF psychotherapy by 2 points or more on the BDI-II, after adjusting for pretreatment scores and therapist effects. This is equivalent to a standardized ES of 0.2, given the expected baseline SD of 10 for the BDI-II. For details, see the SAP.

This model can accommodate missing values of the outcome variable at either of the 2 time points included in the analysis. Estimates are valid provided that values are missing at random (MAR) conditional on the other variables included in the model. This procedure has been shown to lead to unbiased treatment effect estimates under the MAR assumption and to more efficient estimates compared with multiple imputation [1,108]. The model will be fitted using restricted maximum likelihood estimation.

Analogous to the primary analysis, we will use a mixed-effects logistic regression model to estimate the difference in recovery rates between blended and FTF psychotherapy, and a mixed-effects linear regression model to estimate the difference in participants’ quality of life.

A number of sensitivity analyses will be conducted:

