Using complete cases only. This amounts to estimating Model 1 on participants who provided valid information on the primary outcome at the 6-month follow-up. To be included in this analysis, participants do not need to have provided information on the primary outcome at the end of treatment. Within this sensitivity analysis, item missingness will be handled as described above.The assumption of equivalence of effect of blended CBT and PDT will be investigated by estimating a model identical to Model 1 in all respects except that we will allow for an interaction between type of therapy and treatment condition.Whether the conclusions from the primary analysis model (Model 1) would hold if we instead estimated separate treatment effects (blended versus FTF) for CBT and PDT, respectively.Adjusting for concerning imbalances in baseline characteristics.Impact of COVID-19. We will document the impact of the COVID-19 pandemic on the delivery of treatments (eg, moving FTF sessions to a remote format), describe the frequency of remote sessions, and conduct exploratory analyses to evaluate whether the difference in effectiveness between the blended and FTF conditions varies depending on whether some FTF sessions were conducted remotely.

Supportive analogous analyses will also be conducted for the 1-year and 2-year follow-up endpoints once they are available after the second database lock, as for the primary endpoint, including all previous endpoints in the linear mixed-effects models.

Furthermore, we will conduct exploratory analyses to determine the shape of the relationship between BDI-II scores and time. On this basis, we will develop a longitudinal mixed-effects model and investigate whether the rate of change in BDI-II differs between (1) blended versus FTF psychotherapy, (2) CBT versus PDT, and (3) the interaction of the two. For the secondary outcomes, we will also explore longitudinal mixed-effects logistic regression to estimate trajectories of recovery rates and longitudinal mixed-effects linear regression to estimate trajectories of quality of life.

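### Unblinded therapists may propose withdrawal from the study on expected nonresponse to the allocated arm, so missing 6-month outcomes can depend on prognosis and arm

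*Protocol article*

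**What the plan says.** Discontinuation and Withdrawal gives three grounds on which a therapist may propose that a patient leave the study. The first begins "Therapists can propose to withdraw a patient from the study (1) if they are of the opinion that a patient risks serious deterioration" and adds, joined by 'and', "nonresponse to the treatment to which they have been allocated"; the article glosses this as a need for longer-term treatment. The second is ineligibility discovered after screening. The third is that participation interferes with treatment, for example because "the patient is overly burdened by having to complete assessments". In every case the therapist must discuss the matter with the patient and "must seek advice from a site supervisor and from the chief investigator". The section ends "Patients who withdraw from the study for any reason are not replaced". It does not say whether outcome assessments continue after withdrawal.

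Other sections bear on this:

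- **Blinding:** therapists cannot be blinded.
- **Randomization:** each therapist treats patients in both formats.
- **Interventions:** a patient who needs more treatment at the end of the program may continue or be referred. The extra care is recorded in the eCRF or through the TIC-P, which Table 1 schedules at the follow-up visits.
- **Primary and Secondary Outcome Analysis:** under intention to treat, "all participants will be analyzed as randomized, even if they dropped out of treatment or changed treatment during the study period". The model accommodates a missing outcome at either of two time points. On validity it says "Estimates are valid provided that values are missing at random (MAR"), given the other model variables. The missing-data sensitivity analysis listed is "Using complete cases only".

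**The concern.** The first ground is a forecast of the patient's outcome, judged against the allocated arm by someone who knows that arm. If assessment stops on that ground, whether the 6-month BDI-II is missing depends on an expected poor outcome. The model variables are baseline BDI-II, therapy type, therapist, center and the other time point. The therapist's forecast is not among them, so missing at random is doubtful for these patients.

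A patient withdrawn before the end of treatment has no post-baseline BDI-II. The model then in effect treats that patient like retained patients in the same arm with the same covariates, which is too favourable.

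The article is also uneven on the same need. A patient found to need longer treatment at the end of the program stays in follow-up under Interventions. A patient for whom this is foreseen earlier may leave the study under Discontinuation and Withdrawal. That is a data-collection rule, which an analysis plan cannot undo. With a margin of 2 points, a shift of a few tenths of a point is enough to change the error rate of the noninferiority test.

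**Working it through.** **Step 1. Reproduce the plan's figure.** Inputs from Sample Size and Power Calculation: margin 2, SD 10, true difference 0, one-sided alpha 0.025, power 80%, within-patient correlation 0.6, therapist ICC 0.05, 36 therapists.

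- Unadjusted: 2 × (1.960 + 0.842)² × 10² / 2² ≈ 393 per arm, 786 in total.
- Adjustment: (1 − 0.6²)(1 − 0.05) = 0.608. 786 × 0.608 = 478, or 13.3 per therapist, rounded up to 14. 14 × 36 = 504.
- SE of the difference at 504: 10 × √0.608 × √(4/504) = 0.695.
- Power: Φ(2/0.695 − 1.96) = 0.82.

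The stated 504 and 82% reproduce. No allowance for withdrawal enters the calculation.

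**Step 2. Bias by formula.** Let w_B and w_F be the shares withdrawn in the blended and FTF arms, and D_B and D_F the mean excess of the withdrawn patients' true BDI-II over the model's prediction. The article gives none of these, so all are assumptions.

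Bias = −(w_B·D_B − w_F·D_F)

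Error at a true difference of 2 = Φ(−bias/SE − 1.96)

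Take w_B = 10% and w_F = 5%. On average 7.5% are lost, leaving 504 × 0.925 = 466, so SE = 7.797 × √(4/466) = 0.722.

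| D in both arms (points) | Bias | One-sided error |
|---|---|---|
| 4 | −0.2 | 4.6% |
| 8 (about one residual SD) | −0.4 | 8.0% |
| 12 | −0.6 | 12.9% |

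If the arms are exchanged, the signs reverse. With equal w and equal D the bias is 0. Equal rates alone are not enough: 10% in each arm with D_B = 8 and D_F = 4 gives −(0.8 − 0.4) = −0.4.

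The bias does not depend on N. At the 463 enrolled, the 10% versus 5%, D = 8 case has SE = 7.797 × √(4/428) = 0.754 and error Φ(0.4/0.754 − 1.96) = 7.6%.

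**Step 3. Simulation.** 2,500 replications per scenario, N=504, 36 therapists, true difference 2, therapist-adjusted ANCOVA. Withdrawal is driven by a therapist judgement correlated 0.3 or 0.6 with the true 6-month residual; end-of-treatment and 6-month residuals correlate 0.7. All three correlations are assumptions. Ranges run over the two judgement correlations.

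| Withdrawn, blended vs FTF | End-of-treatment BDI-II | Bias (points) | One-sided error |
|---|---|---|---|
| 5% vs 5%, 10% vs 10% | missing or observed | about 0 | 2.5–3.4% |
| 10% vs 5% | missing | −0.17 to −0.38 | 4.5–9.0% |
| 10% vs 5% | observed | −0.11 to −0.21 | 4.0–5.1% |
| 15% vs 5% | missing | −0.41 to −0.75 | 9.5–20% |
| 15% vs 5% | observed | −0.18 to −0.40 | 3.7–8.6% |

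With no withdrawal the simulated error was 2.3% to 3.0%, which shows the simulation noise. An observed end-of-treatment score removes about a third (1 − 0.110/0.169 = 35%) to just over half (1 − 0.180/0.410 = 56%) of the bias.

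**The case against.** The strongest reply is that the article asks for more than a therapist's opinion, and that nothing in it shows a bias in either direction. Much of that stands.

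- **Safeguards.** A reader might infer that therapists can remove nonresponders on their own. They can only propose. The patient must be consulted and senior advice sought, and the ground requires expected serious deterioration and nonresponse together. The advice is not described as blinded or binding, so the route to selective loss narrows but stays open.
- **Direction.** A reader might infer that the bias runs toward a false noninferiority claim. The document does not support that. Treatment length is similar in the two formats, and every therapist treats both, balanced within therapist. Lack of blinding makes an imbalance possible but does not fix its sign.
- **Assessments stop.** This is implied by the third ground, where assessment burden is a reason to leave. It is not stated for the first two.
- **The model cannot help.** Too absolute. Where the end-of-treatment BDI-II exists, the model recovers part of the loss.
- **Intention to treat is contradicted.** It is not. That statement covers treatment dropout and change and is silent on study withdrawal. Outcomes missing under a declared assumption are a limitation, not a conflict.
- **No missing-not-at-random analysis.** The article refers to a detailed SAP that is not shown, so its absence from the article is no finding.
- **Timing.** Recruitment ended on December 2, 2024 and the primary data lock is set for October 2025. A change in data collection now chiefly helps later visits.

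**Conclusion.** The point holds in a limited form. Discontinuation and Withdrawal contains a rule under which an unblinded judgement of prognosis can lead to missing primary outcomes, and that judgement lies outside the missing-at-random model. The rule sits awkwardly beside Interventions and the intention-to-treat statement, and the passages should be reconciled.

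The effect on the trial is a risk of unknown size and sign. Under an assumed 10% versus 5% loss at N=504, the simulations put it at about 0.1 to 0.4 points, or 5% to 20% of the margin, with one-sided error of about 4% to 9%. Larger imbalances do more harm, and balanced withdrawal does essentially none. These figures rest on assumed rates, on the assumed accuracy of therapists' judgement, and on assessment ending at withdrawal. They do not show that the trial is biased or that it leans toward noninferiority. The correction is worth making because it is cheap and lowers the risk, but the point does not by itself invalidate the primary analysis.

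**What to change.** 1. Reconcile Discontinuation and Withdrawal with Interventions and with the intention-to-treat statement. Say that a therapist-proposed withdrawal on the first or second ground does not end scheduled outcome collection unless the patient withdraws consent to it. Apply this to all visits still due, mainly the 1-year and 2-year follow-ups before the second lock expected in March 2027.
2. For the primary endpoint, report withdrawals by arm, by who initiated them and by reason, and whether an end-of-treatment BDI-II was obtained.
3. If the SAP has no missing-not-at-random analysis, specify before unblinding an arm-specific delta-adjusted tipping-point analysis, alongside the complete-case analysis. Shift the missing outcomes separately in each arm, with the largest shifts for therapist-proposed withdrawals, and report the shifts at which the noninferiority conclusion changes. Complete cases alone do not relax the missing-at-random assumption.

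The cost is a short amendment, a few more questionnaires from patients who agree to complete them, and one extra analysis. No view is taken on the clinical grounds for ending treatment.
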